### Data Management and Protection

All trial data will be collected via the MIND-APP framework. The database server will be behind a virtual private network with a firewall, requiring a combination of username, password, and certificate for access. Access to the database system further requires a username and password. An automatic audit trail will log all data access.

Directly identifiable information, including name and phone number, will be recorded at the informed consent stage and will be stored separately from the trial data, encrypted, and stored on servers compliant with Norwegian data protection regulations (GDPR [General Data Protection Regulation] and Norwegian Personal Data Act). Identifiable information will be required for 2 primary purposes:

To ascertain that all participants are real personsTo reduce the risk of repeat registrations, both for eligible and ineligible individuals

For participants eligible to receive compensation in the form of gift card vouchers, the name and phone number will be retained to comply with accounting regulations.

The link between the directly identifiable information and trial data will be deleted upon completion of data collection and prior to analysis.

Anonymized data will be retained indefinitely for research purposes.

Study materials and essential documents (trial master file, analysis datasets, and regulatory correspondence) will be archived by Akershus University Hospital for a minimum of 10 years following trial completion, in accordance with Norwegian research regulations.

### Statistical Analysis Plan

#### Statistical Methods

Observed values from the per-protocol population will be used for the primary analysis. Sensitivity analyses including complete cases and an intention-to-treat analysis with imputed values will also be conducted. The RCT app automatically records all use of all app functions with timestamps, and per-protocol compliance will be determined as having viewed the 3 primary videos of the Tankevirus and Grubl arms or having completed the 3 primary units of the placebo arm. Participants with compliance below the per-protocol threshold will be included in the intention-to-treat analysis but not the per-protocol analysis.

The primary analysis will use an analysis of covariance (ANCOVA) framework: the postintervention score will be the dependent variable, treatment arm the primary factor, and baseline score a covariate. This adjusts for regression to the mean and improves precision. Stratification variables used in randomization (sex, age group, and symptom severity) will also be included as covariates.

The trial compares 2 separate treatments with placebo, and the literature is divided on whether testing should be adjusted for multiplicity [33]. To account for the 2 treatment-vs-placebo comparisons while controlling the familywise type I error rate, Dunnett procedure will be applied to the ANCOVA-adjusted (least squares) means, exploiting the positive correlation between the 2 test statistics arising from the shared placebo arm [34].

#### Coprimary Outcomes

The coprimary outcomes will be change in GAD-7 sum score between baseline and the postintervention follow-up in participants with a baseline GAD-7 score ≥5, and change in PHQ-9 sum score between baseline and the postintervention follow-up in participants with a baseline PHQ-9 score ≥5. Secondary analysis will examine differences between baseline and the 3- and 6-month follow-up using a general linear model or a comparable suitable method, including stratification for available baseline characteristics.

#### Secondary Outcomes

Secondary outcomes WSAS and EQ-VAS will be compared between baseline and the 3 primary follow-up time points (4-week, 3-month, and 6-month) in the same manner as the primary outcome.

EQ-5D-5L will be used to determine differences in accrual of QALYs between the trial arms using Norwegian population preference weights. The primary QALY analysis will include only the observed period, with separate analyses using extrapolation to 1- and 3-year time horizons.

The score on the EQ-5D-5L anxiety and depression dimension will be analyzed as a separate measure in the same way as the primary outcome.

The proportion of participants reporting worsened symptoms and treatment-emergent adverse events will also be compared.

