#### Outcome Measurement Instruments

The GAD-7 is a 7-item self-report scale developed to assess the severity of generalized anxiety disorder symptoms [19]. It is widely used as a brief screening and outcome measure for anxiety in clinical practice and research [20,21]. Measured at baseline, postintervention, and at 3- and 6-month follow-up. Items are scored 0 to 3 (total score 0 to 21). Cutoffs: 5 (mild), 10 (moderate), and 15 (severe). Excellent reliability (Cronbach α≥0.92).

The PHQ-9 is a 9-item self-report instrument designed to assess depressive symptom severity based on *DSM-IV* (*Diagnostic and Statistical Manual of Mental Disorders* [Fourth Edition]) criteria [22]. It is a commonly used tool for depression screening and monitoring treatment outcomes in research and practice [23,24]. Items are scored 0 to 3 (total score 0 to 27). Cutoffs: 5 (mild), 10 (moderate), 15 (moderately severe), and 20 (severe). Measured at baseline, postintervention, and at 3- and 6-month follow-up.

The EQ-5D-5L, developed by the EuroQol Group [25], measures HRQoL across 5 domains (mobility, self-care, usual activities, pain/discomfort, and anxiety/depression) with 5 severity levels. It is extensively used in clinical trials, health economics, and QALY calculations [26]. The Norwegian EQ-5D-5L tariff will be used. Delta QALYs will be calculated using interpolation over the 6-month observation period. The EQ visual analog scale (EQ-VAS; 0-100) captures self-rated health. Utility values for QALY calculation will use the Norwegian EQ-5D-5L value set [27]. Measured at baseline, postintervention, and at 3- and 6-month follow-up.

The Work and Social Adjustment Scale (WSAS) is a 5-item self-report scale developed to measure functional impairment attributable to a specific health problem across work, home management, social and private leisure activities, and relationships [28]. It is frequently used to quantify disability in mental health research and evaluate treatment impact. Scores range from 0 to 40; higher scores indicate greater impairment. A score >20 indicates moderately severe or worse impairment. Measured at baseline, postintervention, and at 3- and 6-month follow-up.

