#### Health Economic Evaluation

A health economic evaluation will be conducted from the perspective of the public health services. Differences in QALY accrual, as indicated by EQ-5D-5L, will be combined with cost estimates for the apps (no costs assigned to the placebo app) and costs related to reported health services resource use. A standard economic evaluation framework will be used to calculate ICER between the placebo arm and the 2 apps (technically, analyses will compare all 3 apps, as they will be conducted prior to disclosure of which data arm corresponds to which trial arm) [35].

The economic evaluation will follow CHEERS (Consolidated Health Economic Evaluation Reporting Standards) 2022 reporting standards and International Society for Pharmacoeconomics and Outcomes Research (ISPOR) guidelines for economic evaluation of digital health interventions. QALYs will be calculated as the area under the utility curve using linear interpolation between measurement points (baseline, 4 weeks, 3 months, and 6 months), with utilities derived from the Norwegian EQ-5D-5L value set. Unit costs for Norwegian health care services will be sourced from the Norwegian Medical Products Agency. Intervention costs will be estimated as total development and maintenance costs divided by a range of plausible numbers of users completing the app, assuming that the apps would not be substantially revised within the relevant time frame from release. Cost-effectiveness acceptability curves and net health benefit analyses (Stinnett-Mullahy framework) will be used to characterize decision uncertainty under varying willingness-to-pay thresholds.

In addition to the primary economic analysis over the observed 6-month trial period, exploratory extrapolated analyses to 1-year and 3-year time horizons will be conducted using parametric models fit to the observed utility trajectory to inform long-term cost-effectiveness estimates.

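### The plan carries the QALY difference into the ICER without naming an adjustment for baseline EQ-5D-5L utility, and leaves 'Delta QALYs' undefined

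*Protocol article*

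**What the plan says.** All references are to the protocol article.

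- **Construction of the QALY.** Health Economic Evaluation: "QALYs will be calculated as the area under the utility curve using linear interpolation between measurement points", with utilities at baseline, 4 weeks, 3 months and 6 months. Outcome Measurement Instruments uses another term: "Delta QALYs will be calculated using interpolation over the 6-month observation period". It does not say whether delta means change from baseline or the increment between arms.
- **Comparison of QALYs.** Secondary Outcomes, within the analysis plan: "EQ-5D-5L will be used to determine differences in accrual of QALYs between the trial arms using Norwegian population preference weights". No model or covariate follows.
- **Use of the difference.** Health Economic Evaluation: "Differences in QALY accrual, as indicated by EQ-5D-5L, will be combined with cost estimates for the apps", and then "A standard economic evaluation framework will be used to calculate ICER between the placebo arm and the 2 apps".
- **Treatment of other outcomes.** In Statistical Methods, the primary analysis is an ANCOVA in which "the postintervention score will be the dependent variable, treatment arm the primary factor, and baseline score a covariate", with the stratification variables added. The reason given is "This adjusts for regression to the mean and improves precision". Secondary Outcomes has WSAS and EQ-VAS compared "in the same manner as the primary outcome" and applies the same approach to the EQ-5D-5L anxiety/depression dimension. The QALY paragraph stands between these two statements and has no such wording.
- **Availability of the covariate.** Table 1 schedules EQ-5D-5L at enrollment. Utility is not among the stratification factors, which are sex, age group and baseline symptom severity.

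**The concern.** Two outputs of the EQ-5D-5L questionnaire (EQ-VAS and the anxiety/depression item) are assigned a baseline-adjusted analysis. The output that decides the economic question is not. The plan's own reason for adjusting, regression to the mean and precision, applies to utilities just as it does to symptom scores.

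Baseline utility enters the area directly and also predicts every later utility. A chance difference between arms at baseline therefore passes into the QALY difference. If delta QALYs means the area minus baseline utility carried forward for six months, the baseline is subtracted with a coefficient of 1, which over-corrects whenever the correlation between visits is below 1.

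Incremental QALYs over six months are likely to be small. As an illustration only, a sustained utility gain of 0.03 is worth 0.03 × 0.5 = 0.015 QALY. The sample size rests on GAD-7 and PHQ-9, so QALY precision has no designed reserve.

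**Working it through.** **The plan's own figures.** The article gives no utility SD, correlation or target QALY difference, so there is no QALY figure to reproduce. The single-outcome sample size (d = 0.3, 80% power, α = .05) does reproduce: 175 per arm by the normal formula, and 175.4 by the t test, which rounds up to the stated 176. It does not bear on QALYs.

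**Inputs.** From the article: visits at 0, 4 weeks, 3 months and 6 months, and 300 per arm (Sample Size Calculation). Assumed: the same utility SD *s* at every visit (0.15 to 0.25) and the same correlation ρ between all visits (0.4 to 0.7).

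**Weights.** Linear interpolation at 0, 4/52, 0.25 and 0.5 years gives w = 0.0385, 0.125, 0.2115, 0.125. The sum is 0.5 and Σw² = 0.0775. Baseline has 0.0385/0.5 = 7.7% of the weight.

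**Formulas**, with variances in units of s²:
- Slope of the area on baseline utility: b = 0.0385 + ρ(0.5 − 0.0385)
- Raw area: V_raw = (1 − ρ)Σw² + ρ(0.5)²
- Adjusted for baseline: V_adj = V_raw − b²
- Area minus 0.5 × baseline utility: V_delta = V_adj + (b − 0.5)²

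**Worked case, ρ = 0.5.** b = 0.0385 + 0.5 × 0.4615 = 0.269. V_raw = 0.0387 + 0.125 = 0.1637. V_adj = 0.1637 − 0.0725 = 0.0913. V_delta = 0.0913 + 0.231² = 0.1445. With s = 0.20, the standard error of the difference is √(2 × V × 0.04/300): 0.0066 raw, 0.0062 delta, 0.0049 adjusted.

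| ρ | b | V_raw | V_delta | V_adj | Cut vs raw | Cut vs delta |
|---|---|---|---|---|---|---|
| 0.4 | 0.223 | 0.1465 | 0.1734 | 0.0967 | 34% | 44% |
| 0.5 | 0.269 | 0.1637 | 0.1445 | 0.0913 | 44% | 37% |
| 0.6 | 0.315 | 0.1810 | 0.1156 | 0.0815 | 55% | 29% |
| 0.7 | 0.362 | 0.1982 | 0.0867 | 0.0675 | 66% | 22% |

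The percentages do not depend on s. As interval width, the cut against the raw area is 1 − √(1 − 0.34) = 19% to 1 − √(1 − 0.66) = 42%.

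**Effect of chance imbalance.** One standard error of baseline imbalance is s√(2/300), or 0.0163 at s = 0.20. It moves the raw difference by 0.0163 × b, which is 0.0036 to 0.0059 QALY. It moves a change-from-baseline difference by 0.0163 × (b − 0.5), which is −0.0045 to −0.0023. Over s = 0.15 to 0.25 the sizes are 0.0027 to 0.0074 (raw) and 0.0017 to 0.0057 (delta). Regression on baseline utility removes this shift.

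**Sensitivity.**
- First follow-up at 2 weeks, which the program lengths allow: the variance ratio raw/adjusted is 1.42 to 2.71 (cuts of 30% to 63%), and delta/adjusted is 1.78 to 1.28 (44% to 22%).
- Baseline-to-follow-up correlation 0.5 to 0.7 with 0.65 between follow-ups: cuts of 39% to 68% against raw and 32% to 24% against delta. The upper end is strained, because baseline would then predict later visits better than follow-ups predict each other.

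**The case against.** The strongest reply is that the text is silent and not wrong. An area under the curve is how each participant's QALY is built, and it is also the dependent variable of the regression recommended here. Nothing in the article excludes covariates. It points to a standard economic evaluation framework, CHEERS and ISPOR guidance, and a fuller analysis or health economic plan may exist. This reply stands in part, and it rules out three stronger readings that a reader might infer.

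1. **That the plan prescribes a raw or change-from-baseline comparison.** It states no comparison model. 'Delta QALYs' may simply mean the increment between arms, which would fit the wording of the other two sections.
2. **That QALYs are the only outcome without baseline adjustment.** The Coprimary Outcomes section gives GAD-7 and PHQ-9 at 3 and 6 months a general linear model or similar, without naming the baseline score as covariate. Worsening and adverse events are only said to be compared. CSQ-8 and SUS have no baseline measurement.
3. **That the ICER would be biased.** Under randomization, chance imbalance is variance. An unadjusted standard error and acceptability curve already contain it, and the one-standard-error shift (0.0044 at s = 0.20, ρ = 0.5) is smaller than the raw standard error (0.0066). Minimization on symptom severity may reduce the imbalance somewhat.

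The contrast inside the plan still remains. It gives a reason for baseline adjustment, applies it by name to neighbouring outcomes from the same questionnaire, and omits it for the quantity that enters the ICER. Two unlinked terms for that quantity are a defect of the article itself.

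**Conclusion.** The point holds as a matter of precision and clarity. Followed as written, the plan permits an unadjusted QALY difference, which is unbiased but less efficient than the baseline-adjusted one. The size of the loss rests wholly on assumed correlations, equal at all visits, so the figures show an order of magnitude and are not estimates for this trial. The direction is robust: in every scenario examined, adjustment was more precise than either alternative. QALYs are a secondary outcome and the coprimary conclusions are not affected. Cost-effectiveness is nevertheless a stated aim of the trial, so the improvement is worth making before recruitment starts.

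**What to change.** In Secondary Outcomes (analysis) and Health Economic Evaluation, state that incremental QALYs are estimated by regressing each participant's 6-month area on arm, baseline EQ-5D-5L utility and the stratification factors (sex, age group, symptom severity). State that this adjusted estimate is the one used in the ICER, net health benefit and acceptability curves. Costs and QALYs must be handled jointly, so the adjustment belongs inside the joint procedure, for example a bivariate regression or a bootstrap that refits the model in each replicate.

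In Outcome Measurement Instruments, define 'Delta QALYs' as the adjusted between-arm increment in the area, or drop the term.

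The cost is a few sentences and some analysis code. No new data are needed, and the article schedules the trial launch for September to December 2027, so the change can still be prespecified.

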#### Health Economic Evaluation

A health economic evaluation will be conducted from the perspective of the public health services. Differences in QALY accrual, as indicated by EQ-5D-5L, will be combined with cost estimates for the apps (no costs assigned to the placebo app) and costs related to reported health services resource use. A standard economic evaluation framework will be used to calculate ICER between the placebo arm and the 2 apps (technically, analyses will compare all 3 apps, as they will be conducted prior to disclosure of which data arm corresponds to which trial arm) [35].

The economic evaluation will follow CHEERS (Consolidated Health Economic Evaluation Reporting Standards) 2022 reporting standards and International Society for Pharmacoeconomics and Outcomes Research (ISPOR) guidelines for economic evaluation of digital health interventions. QALYs will be calculated as the area under the utility curve using linear interpolation between measurement points (baseline, 4 weeks, 3 months, and 6 months), with utilities derived from the Norwegian EQ-5D-5L value set. Unit costs for Norwegian health care services will be sourced from the Norwegian Medical Products Agency. Intervention costs will be estimated as total development and maintenance costs divided by a range of plausible numbers of users completing the app, assuming that the apps would not be substantially revised within the relevant time frame from release. Cost-effectiveness acceptability curves and net health benefit analyses (Stinnett-Mullahy framework) will be used to characterize decision uncertainty under varying willingness-to-pay thresholds.

In addition to the primary economic analysis over the observed 6-month trial period, exploratory extrapolated analyses to 1-year and 3-year time horizons will be conducted using parametric models fit to the observed utility trajectory to inform long-term cost-effectiveness estimates.

### Additional and Exploratory Analyses

Mixed-effects regression models for repeated measures models (mixed model repeated measures) will be used to explore outcomes between trial arms, stratified by demographic characteristics and baseline scores.

Logistic models will be used for binary outcomes and Gaussian models for continuous outcomes.

All analyses will be conducted in R (R Foundation for Statistical Computing). Analysis code will be publicly available with the stage 2 submission as part of the open science commitments of this registered report.

No formal interim efficacy analyses are planned for this trial. The trial may be terminated early if recruitment is insufficient to meet the target sample, subject to agreement from the principal investigator and sponsor (Akershus University Hospital). In the event of an unexpected safety signal, the Trial Oversight Committee/Data Safety Monitoring Board has the authority to recommend early termination.

Considering the brevity of the interventions, no individual discontinuation rules are defined. Patients who report symptoms that would exclude them from participation will be provided the same information on places to seek help as patients excluded (Multimedia Appendix 4).

### Risk Management and Participant Safety

Participants will be screened at baseline for suicidality. Those with severe symptoms or risk will be excluded and directed to appropriate services. The study app will include links to national helplines. Adverse events will be monitored and documented using a structured reporting system within the app.

A data safety monitoring plan will include:

Weekly review of adverse events by the study teamDefined escalation procedures for serious adverse events

### User and Stakeholder Involvement

Both Tankevirus and Grubl were codeveloped with lived experience experts, and this project continues that strong commitment to coproduction.

A coresearcher with lived experience of mental health challenges and expertise in digital mental health services is part of the project group and will colead the development of the placebo app. The coresearcher will also participate in a panel with lived experience of mental health challenges. The panel will meet once per project phase (and additionally as needed) and provide structured feedback and advice on:

Recruitment materials and strategiesUse of incentivesUsability and acceptability of both the RCT app and the placebo appInterpretation of findingsDissemination strategies

Embedding lived experience at multiple levels ensures that the study is ethically sound, scientifically rigorous, and directly relevant to those it seeks to benefit.

Design of a placebo condition that is credible yet ethically sound (addressed through provision of general wellness content and posttrial access to active interventions);Use of financial incentives to improve adherence (gift cards or vouchers following completion); andHandling of personal and sensitive data in accordance with GDPR and Norwegian regulations.

## Results

Funding for this project was approved by the DAM foundation April 28, 2025, conditional on submission of a stage 1 protocol for a registered report by September 15, 2025.

The project timelines, described in a Gannt chart in Multimedia Appendix 5, include submission of the stage 1 protocol in September 2025, followed by finalization of protocol modifications, ethical approval, licensing, and approval of all included instruments from September 2025 through May 2027. Development and testing of Tankevirus version 2.0 is expected to be completed by the end of May 2027. Development and testing of the MIND-APP RCT app will take place from June 2026 to September 2027, alongside final testing from August to November 2026 and pilot testing of the placebo app during the same period. The MIND-APP RCT will launch between September and December 2027, with recruitment and enrollment occurring concurrently. Data collection will run from the start of data collection until 6 months after the final participant has started, no later than August 2028. Analyses are scheduled from August to October 2028, with allocation disclosure in October 2028, followed by final write-up and submission of the stage 2 manuscript toward the end of 2028.

## Discussion

### Principal Findings

This report presents the design and protocol for MIND-APP, a 3-arm RCT evaluating 2 Norwegian self-help smartphone apps; Tankevirus (CBT-based) and Grubl (MCT-based), against a matched digital placebo condition. Registering the protocol prior to data collection ensures analytical transparency and mitigates outcome reporting bias, a recognized strength of the registered report format.

We anticipate that participants in both active arms will show clinically meaningful reductions in anxiety (GAD-7) and depression (PHQ-9) compared with the digital placebo at 4 weeks, with effects potentially sustained at 3- and 6-month follow-up. Given the widespread use of both Tankevirus and Grubl in Norway, with an earlier version of Tankevirus alone reaching approximately 4% of the population, even a modest demonstrated effect would have substantial public health implications. The health economic evaluation will address whether either app represents cost-effective resource use from a Norwegian public health perspective.

